## **1. GENERAL INFORMATION**

### **1.1. Title**

Effects of stress and simulation on team performance during management of an infant in shock

## **2. SCIENTIFIC JUSTIFICATION AND GENERAL DESCRIPTION OF THE STUDY**

### **2.1. Denomination and description of the clinical situation**

We shall set an "infant in shock" as a model for professional stress during management by a multidisciplinary team.

### **2.2. Background information**

An infant of six months, held in the arms of his parents, was admitted into an acute, level one (high priority) emergency room ("salle d'accueil des urgences vitales [SAUV]"), for hypovolemic shock following dehydration, in a context of acute gastro-enteritis. The medical team, of which the leader was a young doctor, was facing tremendous stress due to the impossibility to establish a peripheral venous access despite numerous attempts. The insertion of an intraosseous access (IO), recommended procedure in this context (Biarent 2010), was not evoked by lack of competence in this procedure. What was there to do? The lethal prognosis of this child was overturned following reinforced assistance by a physician trained in the practice of IO access, which allowed to establish a rapid volume expansion, and thus ensure the treatment of this type of shock.

How can one guarantee the security of such an infant in shock after being admitted into a level one (high priority) emergency room? This clinical case well reflects the three elements that are involved in the safety of a patient: the mastery of a technical skill (success rate or efficiency), such as IO access performance (Oriot 1994), the respect for algorithms (effectiveness) (Biarent on 2010) and the quality of teamwork (Eppich 2008). Performance is the resultant of these elements, all indispensable so as to obtain maximal security for the patient.

Management of an infant in life-threatening distress corresponds to a complex clinical situation where the main objective is to coordinate and accomplish numerous procedures, which involve several actors, who will proceed according to a pre-established algorithm, determined by international recommendations. Performance, that is, the global quality of management, depends not only on actions taken according to an algorithm but, also, on the quality of teamwork necessary to best coordinate management of the patient (Rosen 2008). Stress, generated by the fact that the situation evolves an infant in life-threatening distress, is a factor that can modify all these parameters - control of mastered technical skills, respect of algorithms and coordinated teamwork - and, by consequence, affect global performance in management of such a case.

### **2.3. Teamwork**

One of the constituent characteristics of a team is that its members are required to interact with each other so as to successfully realize a team task (Beaubien 2004). Teamwork becomes a crucial element for effective patient care. Unfortunately, only few courses have focused on training towards effective teamwork (Shapiro 2008). Education targeting teamwork can establish a more collaborative working style within a group of clinicians, so as to improve patient safety (Morey 2002). Functioning within a team imposes technical competencies such as distribution of tasks, control of communication, awareness of the situation and decision-making within a team (Yee 2005). Research in the field of non-technical skills led towards the development of scales evaluating behavior and communication. Among the existing tools, the CTS - Clinical Teamwork Scale - was used and validated in emergency situation simulations, and showed excellent interobserver reproducibility, accounted for by an intra-class coefficient of correlation = 0.98 (Way 2008).

Furthermore, strong and effective team leadership is absolutely necessary to attain higher performance levels, because team leaders have a triple role: to develop team spirit, to resolve problems they are presented with, and, finally, to motivate teamwork. Competencies required to be a leader consist of a clear perception of team dynamics,

an understanding of personal interactions impact, and the importance of communication on team function (Shapiro 2008). Teaching leadership is highly insufficient for the time being, and deserves to be further developed so as to attain a degree of excellence. Evaluation of leadership is complex - in simulation, a frequently used scale is that of BAT - Behavioural Assessment Tool (Anderson 2010).

## 2.4. Stress

The effect of stress on a medical team during emergency management of patients must be considered, in that it compromises the security of patients (Gaba 2002). Stress covers all the biologic, electro-physiological and psychological disturbances that may be provoked by an aggression of some kind on the body. Stress provokes an emotional response - in particular, acute anxiety - as well as an alteration of cognitive processes (Kirschbaum 1996, Wolf 2003). The aeronautical industry has long ago admitted to the effects of stress on performance, with risks of decreased performance and human error (Kohn 2000, Loewenthal 2000). Performance losses were also reported in military and sports domains (Driskell 1991, Anshel 2002, Wallenius 2004). Stress decreases recognition of errors, by loss of continuous attention. It increases unsuitable answers during critical management (Sexton 2000). On the other hand, recognizing errors and factors of stress, associated to simulation-based training, improves aeronautical team performance and thereby increases passenger security (Sexton 2000).

Stress has an important psychological effect. Post-traumatic stress state (PTSS) is a frequent pathology in clinical psychiatry, and in persons having undergone one (or more) traumatic event(s) during their lifetime (Yao 2003). One of the scales for evaluating the impact of post-traumatic stress one month later is the Post-traumatic Check List Scale (PCLS), which allows for a reliable approach of PTSS by auto-evaluation (Weathers 1993). There are other validated stress evaluation scales in English, translated and validated in French, such as the IES-R - Impact of Events Scale-Revised, very widely used by and recognized at an international level (Brunet 2003). The latter was created by Weiss and Marmar in 1996, based on Horowitz's Impact of Event Scale (Horowitz 1979), which was translated and validated in French by Brunet in 2003 (Laurent 2007). IES-R measures the presence of traumatic stress connected to recent, traumatizing events. The initial version of Horowitz's scale consisted of two axes: avoidance and repetition behaviour associated to traumatic symptomatology. In 1996, Weiss and Marmar added a third dimension: neurovegetative hyperactivity. Twenty two items thus evaluate the intensity of each symptom, using a Likert type scale ranging from "extremely" to "not at all" (Laurent 2007). The IES-R scale was validated by using numerous accident or aggression victims. It differentiates well subjects in a state of acute stress from presenting post-traumatic stress (Brunet 2003). A score of 22 would be indicative of an acute stress whereas a score of 36 would suggest the presence of PTSS, without, however, providing any diagnosis (Brunet 2003).

Professionals subjected to acute stress causes them to implement various stress management strategies (Anshel 2002). It was demonstrated that bad stress management has negative effects, notably in performance (Hassan 2006). It was recently reported in simulation studies, that the management of surgeons' stress was independent from any professional experience (Wetzel 2010). This particular team used an interview method of those involved, following simulation, so as to determine which of 6 predefined stress management strategies were applied.

Stress induces biologic modifications such as the increase of cortisol in the body. Just as blood plasma cortisol, so salivary cortisol is a faithful reflection of stress, with the major advantage that it does not require invasive sampling techniques (Weibel 2003). Salivary cortisol is a good biologic marker of acute stress, and has been measured in a number of stress models (Schreinicke 1990, Wagner 2010). It is frequently used to monitor athletes: it is more elevated during or right after a competition, as compared to training sessions, regardless of the athlete's competition level (Maso 2002). This rise in salivary cortisol seems to be connected to physiological and psychological stress during a competition (Filaire 1997). Also, in models of long-term stress, such that of being exposed to road traffic noise (Wagner on 2010) or plane motion (Berthon 2001), it has been reported that there is a significant increase salivary cortisol concentrations.

Stress is also at the source of physiological disturbances, such as rise in arterial blood pressure, acceleration of heart rate and modification in its variability and electrocardiographic RR' interval. A number of variables can be measured by Holter and indicate the presence of stress: blood pressure, average heart rate (HR) and its variation, variation in statistical standard deviation of average HR, percentage of RR' intervals > 500 ms, Variability Index (percentage of the average difference between two successive RR' intervals), combined indices such as pNN50, ASDRR'/5 (measurements of RR' using mean standard deviations on 5 minute intervals) and the SDARR '/5 (standard deviations of average RR' on 5 minute intervals) (Anonymous 1996, Task Force 1996). Analysis of the RR' interval is an effective non-invasive method to estimate the autonomous nervous system under conditions of stress (Zheng 1997). A correlation has been established between the state of stress and a decrease of the RR' interval (Sloan 1994). The global effect of stress, confirmed by an increase of salivary cortisol, consists of an increase in blood pressure and a decrease in the RR' interval (Lucini 2002). This marker was also used to assess the effect of stress on individuals with no cardiovascular pathology, and its causation of increased arterial blood pressure, such as what would occur in everyday real life stress conditions (Lucini 2005). Furthermore, the RR' interval has also been correlated with the effect of the stress in individuals with no cardiovascular pathology, but responsible for an increase in blood pressure, such as what would occur in everyday real life stress conditions

(Lucini 2005), or in per-anesthesia states, allowing for assessment, *a contrario*, of the depth of sedation (Nishiyama 2010).

In medicine, the effect of stress on professionals has until now been underestimated. Self-assessment of stress can be evaluated by the Stress-O-Meter (SOM) score (Olpin 2010). Some even deny any errors committed under the effect of the stress, during patient management, in contrast to aviation contexts (Sexton 2000). Certain authors were able to prove a state of post-traumatic stress in Emergency Medical Assistance (SAMU) personnel in France (Laurent 2007, Vaiva 2008), notably using the IES-R scale (Horowitz 1979, Brunet 2003, Craemer 2003). Quite recently, it was demonstrated, in simulation, that stress (assessed by a questionnaire, heart rate variability and salivary cortisol concentrations) altered surgical performance, and was a key element in the quality of care (Wetzel 2010). This team used a questionnaire for a self-assessment of stress, so as to analyze underlying anxiety and anxiety induced by the situation: the STAI - State-Trait Anxiety Inventory, elaborated by Spielberger (Spielberger 1983).

## **2.5. Simulation**

Medical knowledge does not restrict itself to theoretical knowledge, as exhaustive as it may be, it involves, as well, practical know-how, represented by the performance of medical - technical procedures, allowing one to acquire and develop competency and way of being with the surrounding medical team, patients and families. Simulation is an educational tool that allows such learning. Medical simulation is clearly organized in the emergency treatment educational programs of North America (Issenberg 1999, Issenberg 2008). Indeed, in 2009, this learning method has even been recognized by The American Senate (The Enhancing SIMULATION Act of 2009), as the standard method of learning of emergency care ([www.medsim.org](http://www.medsim.org), Forbes and Kennedy 2009). In order to attain a high level of performance, the aptitudes (competence) of everyone involved must be improved. Simulation allows one to attain such an educational objective, by a learning *ex-vivo* (in complete safe conditions for the patient and the operator), and to provide educational evaluations as to the quality of various acquired practical aptitudes (competencies). Even though training on a simulator allows one to reduce errors, it is also more effective to associate entire teams to simulation training (Blum 2004, Birnbach 2008). Simulation allows to improve teamwork, notably in adult (Shapiro 2004) and pediatric (Gilfoyle 2007, Eppich 2008) emergency services.

## **2.6. Summary of benefits, if need be, and predictable risks for those persons lending themselves to the study**

### **2.6.1. Benefits**

#### 2.6.1.1. Individual benefit

The benefit for any given participant in this research study would be to receive, free of any charge, an education by simulation - an innovative practical education, evaluated on medical and relational difficulties faced during management of complex pediatric cases.

#### 2.6.1.2. Collective benefit

Collective profit consists of simulation training of health professionals of the University Hospital of Poitiers and other hospital centers of Poitou-Charentes region in France.

### **2.6.2. Risks**

#### 2.6.2.1. Individual risks

##### 2.6.2.1.1. Risks and physical constraints

Risks related to the participation are those of the discomfort caused by the bearing of a Holter during 24 hours, and the sampling of three salivary samples.

#### 2.6.2.2. Collective risk

None.

#### 2.6.2.3. Expected individual and general adverse effects

None.

### **2.6.3. Benefit / risk ratio**

This study offers a very positive benefit / risks ratio.

**2.7. Statement as to protocol observance, good clinical practices and current legal and statutory measures involved in the framework of this protocol**

The sponsor and the investigator also commit themselves to that this study will proceed:

- According to the protocol,
- According to France's best clinical practices guidelines and recommendations,
- According to current legal and statutory measures in France.

**2.8. Description of the population to be studied**

We shall study multidisciplinary teams consisting of four members each: a senior physician, a junior doctor (resident), a nurse and an ambulance driver.

For each of these statuses, an exhaustive list will be established and will serve for probing. Participants drawn at random will be contacted by e-mail so as to be informed of the study, and to invite them, so as to ask for their consent to participate. (The definitive, signed agreement will be obtained the day before the first session, in the presence of the principal investigator of this study). Modalities as to the drawing of lots are described in paragraph 4.5.1.

### 3. STUDY OBJECTIVES

#### 3.1. Primary objective

**To seek evidence for the existence of stress**, as it will be assessed by three processes throughout the various scenarios:

- Biological stress (Salivary Cortisol [SC]);
- Electrophysiological stress (Holter 24h, timely measures);
- Psychological stress.

#### 3.2. Secondary objectives

**To evaluate performance**, as it will be assessed by three processes:

- Team performance (actions, algorithm, and treatment);
- IO access performance;
- Teamwork and leadership.

**To evaluate the effect of repeated simulation sessions** on performance and stress:

- Performance will be evaluated using the same assessment tools;
- Stress will be investigated by studying the variations of given stress markers and coping responses.

### 4. STUDY DESIGN

#### 4.1. Primary outcome measures

Our primary outcome measure will consist of revealing and evaluating evidence for the existence of stress during the simulation. Such stress will be estimated by 3 different methods:

##### **Biological stress:**

SC will be measured by an Enzyme-Linked Immunosorbent Assay (ELISA) kit (IBL international®, Hamburg, Germany). SC is commonly used to assess stress (Wagner 2010, Beko 2010, Dovio 2010) and this method has been used in simulation (Bong 2010). It will be assessed one day prior to the simulation, just before and right after the simulation session, as well as following debriefing.

##### **Electrophysiological stress:**

Holter parameters (Wilhelm 2005) (HR analysis, temporal and spectral analysis with PNN50 as well as LF/HF ratio) will be obtained using the software Synscope\* (Sorin Group) throughout an entire day (24h recording) - during the resting phase, i.e., sleep, during selective periods at the time of SC sampling, as well as during the phases of simulation, debriefing, and pauses following simulation (Task Force 1996). Timely measures of HR and BP will be associated with this analysis.

##### **Psychological stress:**

will be assessed using 4 self-assessments:

- **Self-assessment** using STAI - *State-Trait Anxiety Inventory* (Spielberger 1983) just before and right after the simulation session, as well as following debriefing.
- Using **SOM self-rating scale** (Olpin 2010). For each self-assessment, participants will be placed in an isolated room so as not to be disturbed.
- **Early post-trauma stress disorder** will be determined on the 7th day following simulation, using IES-R - *Impact of Event Scale-Revised* (Brunet 2003), which will be emailed at that time to each participant.
- **Late post-trauma stress disorder** will be determined one month following simulation, using with PCLS - *Post-traumatic Check-List Scale* (Weathers 1993), which will be emailed at that time to each participant.

#### 4.2. Secondary outcome measures

##### 4.2.1. Evaluation of performance

**Team performance** of a simulated infant shock management will be assessed by three ways:

- **Global team clinical performance** will be evaluated using performance assessment scale ("TAPAS"), designed by the Simulation Laboratory and in validating process (Oriot 2013, unpublished data).
- **IO access procedure process and success** of the insertion technique: evaluated by
  - An assessment scale - IOPAS - *Intraosseous Performance Assessment Scale* (Oriot 2012),
  - Time to decision,
  - And duration of procedure (Oriot 2012) (cf. Appendix).
- **Teamwork performance** will be evaluated using the following validated scales:
  - concerning **Leadership assessment**: BAT – *Behavioural Assessment Tool* (Anderson 2010) (cf. Appendix)
  - concerning **Global Teamwork assessment**: CTS - *Clinical Teamwork Scale*, CTS (Guise 2008) (cf. Appendix)

#### **4.2.2.Evaluation of the effect of repeated simulation sessions on stress and performance**

Effect of repeated simulation sessions on stress and performance will be assessed by the same stress parameters and team performance scores.

To study evolution of stress, we shall calculate the relative variation of different variables obtained from performance scores. Relative variation will be defined by the following calculation:  $([\text{final score}] - [\text{score T0}]) / (\text{score T0})$

We shall study the effect of repeated simulation on the parameters of stress. Finally, the senior physician's stress management strategies will be deduced from previous evaluations and evaluated according to 2 different manners, inspired by the axes proposed by Wetzel (Wetzel 2010):

- Observation during simulation
- Video recording viewing by the supervisors

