### **6.2. Evaluation of the effect of repeated simulation sessions**

Next, we shall estimate the effect of **repeated simulation sessions** on a team's **performance evolution** in terms of safety preservation as concerns an infant in a state of shock, using three parts:

- By estimating the impact of repeated simulation sessions on global team performance (determined by degree of respect for the appropriate algorithm);

University Hospital of Poitiers - CHU de Poitiers Sim-Stress

- By estimating the impact of repeated simulation sessions on insertion of an IO access: insertion technique (evaluation scale), decision-making timing and duration;
- By estimating the impact of repeated simulation sessions on teamwork: evaluation of leadership (evaluation scale) and communication (evaluation scale).

Finally, we shall study the effect of the *repeated simulation sessions* on stress by evaluating various stress markers (biological, electrophysiological and psychological), as well as its impact on stress management strategies. We shall so be able to determine if *simulation session repetition*, expected to improve performance, will be accompanied by high stress levels following implementation of stress management strategies, or if it will be accompanied by a decrease in stress levels. Evaluation of the effect of the *repeated simulation session* will be evaluated by comparison of the 2 groups, i.e. the teams that will participate 9 vs. 3 simulation sessions, as described in paragraph 9

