### **7.2. Description of the parameters involved in the evaluation of stress**

Parameters involved in the *evaluation of stress* will be estimated for every participant, and are described in paragraph 4.2.1

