##### **9.1.4.Comparison of the variation in performance scores between groups 1 and 2 = Evaluation of the effect of repeated simulation on performance**

To study variation in performance (global performance, IO access and teamwork evaluation scores) between the time point of inclusion (T0) and the simulation program's endpoint, the relative variation of various scores will be calculated  $\{([final\ score] - [score\ T0]) / (score\ T0)\}$ . These relative variations will be compared between the 2 groups using a Student's t-test. An ANOVA test will be used to search for a possible effect due to participant status.

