##### **9.1.5.Comparison of stress between groups 1 and 2 = Evaluation of the effect of repeated simulation on stress**

The various stress markers (biological, electrophysiological and psychological) will be compared between the 2 groups 1 and 2 by means of a Student's t test or, if necessary, a Mann-Whitney non parametric test.

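### Section 4.2.2 defines the evolution of stress on performance scores, contradicting 3.2, 6.2, 9.1.4 and 9.1.5, and no section clearly tests the change in stress markers promised in 3.2

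*Protocol*

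**What the plan says.** Section 4.2.2 of the Protocol defines the secondary outcome for repetition. It opens by naming both kinds of variable: "Effect of repeated simulation sessions on stress and performance will be assessed by the same stress parameters and team performance scores". It then states: "To study evolution of stress, we shall calculate the relative variation of different variables obtained from performance scores", and gives the formula (final score − T0 score) / T0 score. After the formula it returns to stress proper: "We shall study the effect of repeated simulation on the parameters of stress".

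Elsewhere in the Protocol:

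- Section 3.2 sets the secondary objective: "Stress will be investigated by studying the variations of given stress markers and coping responses".
- Section 6.2 will study the effect of repetition "on stress by evaluating various stress markers (biological, electrophysiological and psychological), as well as its impact on stress management strategies".
- Section 9.1.4 prints the same formula, introduced by "To study variation in performance (global performance, IO access and teamwork evaluation scores) between the time point of inclusion (T0") and the end of the programme, and compares the result between groups by t-test.
- Section 9.1.5 deals with stress: "The various stress markers (biological, electrophysiological and psychological) will be compared between the 2 groups 1 and 2", by Student's t or Mann-Whitney test.
- Section 7.2 says that the stress parameters "will be estimated for every participant, and are described in paragraph 4.2.1". Section 4.2.1 is the performance section. Section 7.1 sends the reader to 4.1 for the performance scales, and 4.1 is the stress section.

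**The concern.** A section that defines an outcome should say which variables it is built from. Here the one sentence with a formula for stress evolution names performance scores. An analyst who followed it would compute a performance quantity and label it stress.

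What is at stake is the question in section 6.2: whether better performance through repetition goes with persistently high stress or with falling stress. That needs stress and performance to be measured separately, and it needs some account of how stress moves over the programme. The crossed references in 7.1 and 7.2 mean that a reader who looks up the stress parameters to settle the matter is sent to performance scales again.

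**Working it through.** There is no stated figure to reproduce: the point concerns an outcome definition and depends on no sample size, power or alpha. The check is a comparison of sections.

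**1. Which variables stand for stress?**

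| Protocol section | Quantity named | Variables used |
|---|---|---|
| 3.2 | variation of stress | stress markers, coping responses |
| 4.2.2, before the formula | effect on stress and performance | stress parameters and performance scores |
| 4.2.2, formula sentence | evolution of stress | performance scores |
| 4.2.2, after the formula | effect on stress | stress parameters |
| 6.2 | effect on stress | biological, electrophysiological, psychological markers |
| 9.1.4 | variation in performance | performance scores, same formula |
| 9.1.5 | stress, between groups | the three kinds of marker |

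The formula sentence stands alone against all the others. It is best read as a slip, of one of two kinds. Either stress was written where performance was meant, as 9.1.4 suggests, or performance scores was written where stress parameters was meant.

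**2. Does either reading leave stress evolution defined?**

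- If the formula belongs to performance, no formula for stress evolution remains in the Protocol.
- If the formula was meant for stress markers, 9.1.5 does not use it: that section names no change from T0.

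**3. Does a statistical section analyse change in stress markers?**

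- 9.1.2 correlates stress indicators with performance. That is association, not evolution.
- 9.1.3 tests change across sessions by repeated-measures ANOVA or Friedman, for performance scores. Its mixed models on the whole data set are only a possibility, with the emphasis on stress management strategies.
- 9.1.4 tests change from T0, for performance scores.
- 9.1.5 compares stress markers between groups without reference to T0.

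So the markers are analysed, but their variation over the programme is not clearly tested.

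**4. Would the printed ratio suit stress markers?** The ratio is undefined when the T0 value is 0. From the scales as described in the Protocol:

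- SOM runs from 0 to 10 (7.3.2), so 0 is possible.
- IES-R has 22 items scored 0 to 4 (Appendix 9), a total from 22 × 0 = 0 to 22 × 4 = 88, so 0 is possible.
- STAI has 20 items scored 1 to 4 (Appendix 8), a minimum of 20 × 1 = 20, so 0 is not possible.
- PCLS has 17 items scored 1 to 5 (Appendix 10), a minimum of 17 × 1 = 17, so 0 is not possible.

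The ratio also weights equal changes unequally. A one-point rise on SOM from 1 to 2 gives (2 − 1)/1 = 1; from 9 to 10 it gives (10 − 9)/9 = 0.11.

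**5. Are the data there?** Section 4.4.1 repeats the full measurement plan at every session. Group 1 has 9 sessions and group 2 has 3, so both have a first and a last session, and a change from T0 can be formed for all 12 × 4 = 48 planned participants.

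**The case against.** The strongest reply is that this is an editorial slip. The sentences on either side of it, together with 3.2, 6.2 and 9.1.5, all take stress from stress markers, and the statistics section is the operative one. A one-word change in 4.2.2 would bring it into line with 9.1.4. The headings of 4.1 and 4.2.1 are explicit enough that the crossed references mislead few readers. In a randomised comparison, marker levels can validly be compared without a change score, and the choice of session, time point and form of change is often left to the SAP.

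Much of this stands. A reader might infer from 4.2.2 that the stress outcome is simply the performance outcome renamed, that the two would coincide for every team, or that the question in 6.2 cannot be answered. The documents do not support that: 9.1.5 compares the stress markers themselves and uses no performance score, and 6.2 says that the repetition effect is judged by comparing the groups. Nor is it a fault in itself that 9.1.5 omits detail a SAP could supply.

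What does not fall away is that a definition is printed and is wrong. A SAP written from 4.2.2 would inherit the wrong variables. One written from 9.1.5 would find no change to test, although 3.2 promises to study variation.

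**Conclusion.** The point holds as an error of definition with a limited consequence. The formula sentence in 4.2.2 contradicts its neighbouring sentences and sections 3.2, 6.2, 9.1.4 and 9.1.5. The references in 7.1 and 7.2 are swapped. The planned between-group comparison of stress markers survives, so stress is measured and analysed. The variation of those markers is not clearly tested.

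The size cannot be put as a number. A secondary objective is affected; the sample size in 9.2 is not. With 6 teams randomised to each group, a chance difference in stress at T0 is possible. A comparison that ignores T0 remains valid, but it leaves such a difference in the result and does not show whether stress rose or fell. The Protocol gives no variance for any stress marker, so the gain in precision from using T0 cannot be calculated.

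The verdict assumes that stress markers were intended throughout, as every section except this one sentence indicates. It deserves correction before analysis, because the choice of stress measure should not be settled after the data are seen.

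**What to change.** 1. In 4.2.2, assign the relative-variation formula to performance, as in 9.1.4. Add a separate sentence that defines the evolution of stress on the stress markers listed in 4.1.
2. In 9.1.5, compare the final-session stress markers between groups taking the T0 value into account, either as the change from T0 or by adjusting for the T0 value. Do not use the ratio to T0 for scales that can be 0, such as SOM and IES-R.
3. Correct 7.1 to cite 4.2.1 and 7.2 to cite 4.1.

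The cost is a change of protocol wording and slight extra analysis. No new measurement is needed, since the markers are already scheduled at every session.
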